### 9.2.3 Secondary outcomes – GP practice level

Based on NHAIS data, we will explore change (before vs. after) in cervical screening coverage. We will explore variation across GP practice using Funnel plots.

We will run a Mantel-Haenszel test accounting for clustering at the GP practice level to explore the relationship between coverage and before/after.

We will also explore whether coverage varies as a function of age group, screening history, ethnic group and LSOA using change in cervical screening coverage using the extended Mantel-Haenszel test for 2\*j tables so to account for the clusters.

Change in cervical screening coverage at each practice (to assess the impact of self-sampling on coverage):

- Before (including both immediately before the GP practice is “entered” into the trial and exactly one year before the end of the trial) and after the trial.
- Coverage in each month prior to and post the trial starting at the GP practice.

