## 1 BACKGROUND

Cervical screening coverage in England has been falling and is currently at a 20 year low.(1) London consistently has the lowest cervical screening coverage nationally - 64.7% versus 71.4% across England in 2018.(1) Patches in North East (NE) and North Central (NCL) London are amongst the worst performers (age appropriate coverage in Camden CCG 54.6%, Tower Hamlets CCG 60.9% in 2017/18).(2) The North Central and East London Cancer Alliance (NCELCA) commissioned by NHS England to drive local change in the quality of cancer services such as screening, to improve cancer outcomes and patient experience. NCELCA are extremely keen to tackle the issue of falling coverage in their patches.

Currently the most promising solution to this longstanding issue is to offer self-sampling for HPV testing to women who have not attended for screening (i.e. non-attenders). Common barriers to cervical screening include fear or dislike of the pelvic examination, embarrassment, difficulty getting appointments or being too busy.(3-5) Self-sampling addresses most screening barriers enabling women to take a sample themselves, in private and at a time and place of their choosing. There is also robust evidence that offering HPV self-sampling to non-attenders can increase screening uptake, on average by 10%.(6, 7) However, uptake rates are highly variable between studies (6.4%-34%).(6, 8, 9)

In terms of clinical test performance, evidence from an international meta-analysis (including 56 accuracy studies) reported that HPV testing on self-samples are similarly accurate to clinician samples for cervical screening (i.e. for detecting high-grade cervical disease) when using an assay based on polymerase chain reaction.(6, 10, 11) A large non-inferiority trial (the IMPROVE study) that was nested within the Dutch Cervical screening programme showed that primary HPV testing on self-samples in an organised screening setting was non-inferior to clinician-taken HPV samples.(10) In addition, long term (5 year) follow data from a population-based self-sampling study in Scotland show that the risk of CIN2+ and CIN3+ in women with an HPV negative self-sample is extremely very low (0.6% and 0.2%, respectively).(12)

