| To estimate the uptake and increase in coverage associated with offering self-sampling              | 
1. Uptake of kits at 30 days, 90 days and at the end of the trial*
 
2. Change in coverage at participating GP practices (when additionally counting a negative HPV test on a self-sample as having been screened) from the start vs the end of the trial.
 
3. Change in the proportion eligible appropriately screened.
 | 
1. Uptake: number of women screened by self-sample (at 30 days and 90 days from date kit mailed out (from print company) or given out in GP practice (GP records), and total) (from NHAIS and central laboratory) as a % of all women sent kit or opportunistically offered kit (from NHAIS for 15m and from GP record data for opportunistic)
 
2. Coverage: Age-appropriate coverage (as determined by the number of women who have either been screened by cytology or HPV negative on a primary HPV test or self-sample in the past 3.5y if aged 25-49 or 5.5y if aged 50-64y as a % of all those eligible for cervical screening) at participating GP practices. The endpoint is the change in coverage from the (practice-specific) beginning to the (practice-specific) end of the trial (all NHAIS data).
 
3. Eligible women (on the first of each month): women not ceased from screening aged 25-49 who have not been screened within the last 2.9 years or aged 50-64 and not screened within the last 4.9 years.
Appropriately screened: number of eligible women screened within the month. Data will be collected separately for "conventional screen", "return of mailout kit" and "return of opportunistic kit". The proportion eligible screened (by any approach) will be recorded each month during the trial and for the four months before the trial start. The average for the before and after period will be compared.
 |

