#### 4.1.1 Randomisation

If feasible we will randomise the week or month that each GP practice starts the trial (see 18.1 Appendix 1: Randomisation). This is likely only be applied to the start of opportunistic offer (not the mailout). This design is like a form of stepped-wedge cluster randomisation (25) in which more clusters (GP practices) are exposed to an intervention towards the end of the trial than early on. The stepped wedge design helps control for confounding factors (via randomisation) on an intervention which may have an underlying temporal trend. The advantages of using this approach are that it will allow us to assess the impact of offering self-sampling more robustly and make any necessary alterations to the process early on with minimal impact to the majority of the trial sites.

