### **10.4.1 NHAIS dataset**

NHAIS holds the national cervical screening database and is therefore, the most accurate and complete source of screening data. GP records also contain cervical screening data, however, this tends to be less accurate than NHAIS as the two systems are not linked. As such, NHAIS data will be the main source of cervical screening data for the trial

Prior to each data extraction NHS Digital will apply the "exclusion" lists to remove women in the national data opt-out and women who have opted out from data usage for the study (see section 7.3.5). NHS Digital will then extract the data and, prior to sending it to KCL, will encrypt the NHS numbers (i.e. generate study ID) and convert the postcode to LSOA. In this way only anonymous line-level data will be provided to the trial team at King's for all eligible women (i.e. ≥6m overdue cervical screening) and therefore, will include data from women who have not consented to the trial. We will seek CAG approval for this. Data will include:

- Study ID (encrypted NHS number)
- Demographic data (age, LSOA (converted from postcode prior to sending to KCL))
- Cervical screening tests (including self-samples, cytology and HPV tests) dates and results, source of self-sample (opportunistic or mailout) including the last test before trial start, all tests during the trial period)
- Date identified for 15m mail out (if applicable)
- Cervical screening disclaimer returned (i.e. opted-out from the cervical screening programme)
- The woman's GP practice

These line-level NHAIS data will be linked to anonymised line-level data from GP records using the study ID to enable us to assess response rates and cervical screening activity according to ethnicity, whether or not women are offered kits in GP primary care.

We will also collect anonymous aggregate data:

- Practice-specific coverage at before study start, monthly and at the end of the trial

- An additional extract on practice-specific coverage may be requested after the trial has ended (after approximately 13 months after the last kit was handed out) to assess long term coverage.

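### The coverage test named in section 9.2.3 is a before/after comparison with no calendar-time term, so any background change in coverage enters the estimate, and staggered starts proposed to control a trend go unused

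*Protocol*

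**What the plan says.** Section 3.2 lists change in coverage as the second primary endpoint and defines it within practice: "The endpoint is the change in coverage from the (practice-specific) beginning to the (practice-specific) end of the trial". Section 9.2.3, headed as secondary outcomes, states the analysis: "Based on NHAIS data, we will explore change (before vs. after) in cervical screening coverage". The test is then named: "We will run a Mantel-Haenszel test accounting for clustering at the GP practice level to explore the relationship between coverage and before/after". Two further items are listed there. One is a second baseline taken "exactly one year before the end of the trial". The other is a series, "Coverage in each month prior to and post the trial starting at the GP practice". Neither has a model attached.

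Section 4.1.1 proposes to randomise the week or month in which practices start, if feasible, and probably only for the opportunistic offer. Its stated reason is: "The stepped wedge design helps control for confounding factors (via randomisation) on an intervention which may have an underlying temporal trend". The Background gives grounds to expect a trend: "Cervical screening coverage in England has been falling and is currently at a 20 year low".

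Section 10.4.1 lists among the aggregate data to be collected: "Practice-specific coverage at before study start, monthly and at the end of the trial". Time adjustment is specified in section 9.2.2, but for individual-level outcomes only.

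**The concern.** The design section offers staggered starts as protection against a trend, but the analysis section does not use them. A before/after contrast within each practice attributes everything that changes between the two dates to the kits. It never compares practices that have started with practices that have not yet started in the same calendar month.

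Accounting for clustering corrects the variance but does nothing about a trend. The baseline one year before the end matches the season, yet it carries a full year of trend instead of about nine months. The monthly series is indexed to each practice's own start and would show a trend without adjusting for it.

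The first aim in section 3.1 is evidence that self-sampling can improve coverage, and section 9.1 says the trial is there to estimate that increase. A biased estimate of this quantity is therefore a problem even without a formal power calculation.

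**Working it through.** **Reproducing the plan's figures.** The protocol states no expected change, sample size or power for coverage. Its nearby figures do reproduce. Section 9.1.1: 106 practices × 9 months × 20 women = 19,080, stated as about 19,000. Table 2 at 15% uptake: 0.15 ± 1.96 × √(0.15 × 0.85 / 19,000) gives 14.5% to 15.5%, as stated.

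**Size of the gain to be estimated.**
- Practice-weighted coverage from section 5: (33 × 54.6 + 33 × 62.8 + 57 × 63.0 + 36 × 60.9 + 53 × 62.9) / 212 = 61.3%.
- Overdue women in 106 practices, from section 9.1: 0.5 × 190,579 = 95,290.
- Eligible women in 106 practices: 95,290 / (1 − 0.6128) ≈ 246,100.
- Budgeted returns, from section 9.1: about 10,000.
- Gain if every return is HPV negative: 10,000 / 246,100 = 4.1 points. Over the range of CCG coverage (63.0% down to 54.6%) this is 3.9 to 4.8.
- Gain if 85% are HPV negative (an assumption): 0.85 × 4.06 = 3.5 points.

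The separate estimates in sections 9.1.1 and 9.1.2 add to 2,800 + 8,500 = 11,300 returns, which would raise the ceiling to 4.6 points. I use the budgeted 10,000. All of these are gross figures: they assume that no woman who returned a kit would have been screened otherwise.

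**Size of the bias.** The protocol gives no yearly rate, so a range is assumed. Bias = trend × months / 12.

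| Assumed trend (points a year, either sign) | Shift over 9 months | Share of 4.1-point gain | Share of 3.5-point gain | Shift with one-year baseline |
|---|---|---|---|---|
| 0.5 | 0.38 | 9% | 11% | 0.5 |
| 1.0 | 0.75 | 18% | 22% | 1.0 |

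**Simulation.** The set-up was 106 practices with 2,322 women each (246,100 / 106), starts randomised over months 0 to 6, monthly coverage from 4 months before to month 12, and 1,000 runs per scenario with a two-sided 5% test. The level, the between-practice SD of coverage (6 points) and the SD of the practice trend (1 point a year) are assumptions. The comparison model had practice effects, calendar-month effects and months of exposure.

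| True gain | Trend (points a year) | Before/after estimate | Estimate with calendar month |
|---|---|---|---|
| 4.0 | −1.0 | 3.3 | 4.0 |
| 4.0 | −0.5 | 3.6 | 4.0 |
| 4.0 | 0 | 4.0 | 4.0 |
| 4.0 | +0.5 | 4.4 | 4.0 |
| 4.0 | +1.0 | 4.8 | 4.0 |

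With no kit effect, the before/after tests rejected in 64% to 75% of runs at 0.5 points a year in either direction, and in 99% to 100% at 1.0. In both ranges the lower figures are mostly for the practice-clustered test and the higher for the unclustered one. With no trend they rejected in 5% (clustered) and 9% (unclustered). The model with calendar month rejected in about 5% to 6% throughout, with an SD of the estimate of about 0.42 to 0.44 points.

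This is a best case for the model, because both offers were made to start on the randomised date.

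**The case against.** Several points on the other side are fair.

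- **Deferral to the SAP.** Section 9.2 leaves detail to a statistical analysis plan. That would answer a complaint about missing detail. Here the contrast and the test are already named, and an SAP that follows them inherits the bias.
- **Randomisation is conditional.** A reader might infer that the plan discards randomised start dates it is certain to have. The documents do not support that: sections 4.1.1 and 18.1 make randomisation subject to feasibility and probably limit it to the opportunistic offer. The mismatch is between a proposed safeguard and a test that would not use it.
- **Other safeguards.** The before/after test is not all that section 9.2.3 lists. There is also the historical cohort in section 4.1.2 and the monthly proportion screened in section 3.2, split by route. These help interpretation. However, the historical cohort measures screening among overdue women from GP records, not the NHAIS coverage endpoint, and neither is tied to the coverage test.
- **Exploratory wording and status.** Section 9.2.3 speaks of exploring, section 9.1 says the trial estimates rather than tests, and section 9.2.1 names uptake as the primary outcome. The rejection rates therefore matter less than the shift in the estimate. A reader might infer that the trial would almost certainly report a spurious benefit. The documents do not support that: those rates assume no kit effect and an invented trend, and the only direction stated is downward.
- **Limits of the remedy.** Section 4.1 expects mail-out to begin almost at once, while section 7.2.1 admits each practice to mail-out after its training. If all practices begin in one month, time since first mail-out is collinear with calendar month and no model can separate them.

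**Conclusion.** The concern holds in a limited form. Followed as written, the section 9.2.3 test gives a coverage estimate that absorbs any background change, and nothing else listed there removes it. At an assumed 0.5 to 1.0 points a year, the shift over nine months is 0.38 to 0.75 points, roughly 9% to 22% of a gain of 3.5 to 4.1 points. Given the stated fall in coverage, an understated gain is the more likely result.

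The size rests on a trend rate that the protocol does not give, on 10,000 returns, and on 85% to 100% of them being HPV negative. The direction would reverse if coverage were rising. The absence of a time term and of any use of staggered starts is read directly from the text and needs no assumption.

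**What to change.** In section 9.2.3, make the main coverage analysis a model of the monthly practice-level NHAIS coverage already listed in section 10.4.1. Include practice effects, calendar-month effects and time since the opportunistic start, using the assigned date if starts are randomised, with practice-clustered intervals. Add time since first mail-out only if mail-out starts are staggered across practices. If they are not, state that the mail-out effect on coverage cannot be separated from the background trend. Keep the before/after change, with both baselines, as a descriptive result.

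A difference-in-differences against non-participating practices in the five CCGs is optional and supportive only. Those practices select themselves, the communications campaign in section 7.2.3 may reach them, and the extra NHAIS data would need release approval (section 14.4).

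The core change costs wording and a little analysis time. It also costs precision: with an SD of 0.42 to 0.44 points, the 95% interval is about ±0.8 to ±0.9 points (1.96 × SD). At a trend of 0.5 points a year, the bias removed (0.38) is slightly smaller than that SD, so the main benefit there is an interval centred in the right place. At 1.0 point a year the bias removed (0.75) is clearly larger than the SD. The change should be made before coverage data are seen.

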### 9.2.1 Primary endpoint

The primary outcome is uptake which is defined as the proportion of women who return a self-sample at 30 days, 90 days and at the end of the trial amongst those who have been given one direct mail out and opportunistic offer at GP practice with adjustment for multiple testing. We are interested in estimating variability across GP practice by using funnel plots(38) and estimating the intra cluster correlation (ICC).

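### Change in coverage is primary in section 3.2 but secondary in section 9.2.3, and the only test named for it is a before/after Mantel-Haenszel test that cannot separate effect from time trend and has no dependable standard error

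*Protocol*

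**What the plan says.** The Trial Summary and section 3.2 list three primary endpoints. The second reads: "2. Change in coverage at participating GP practices (when additionally counting a negative HPV test on a self-sample as having been screened"), from the start to the end of the trial. The measure adds: "The endpoint is the change in coverage from the (practice-specific) beginning to the (practice-specific) end of the trial". Coverage is the share of all eligible registered women screened within the past 3.5 or 5.5 years, depending on age.

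Section 9.2.1 says "The primary outcome is uptake" and mentions neither of the other two endpoints. It also promises an adjustment for multiple testing. Change in coverage appears only in section 9.2.3, under secondary outcomes, where the named test is: "We will run a Mantel-Haenszel test accounting for clustering at the GP practice level to explore the relationship between coverage and before/after".

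Section 9.2.3 also lists a second baseline one year before trial end and month-by-month coverage around each practice's start. No model is attached to either. By contrast, section 9.2.2 adjusts its individual-level models for time.

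On trend, section 1 states: "Cervical screening coverage in England has been falling". Section 4.1.1 says a staggered start "helps control for confounding factors (via randomisation) on an intervention which may have an underlying temporal trend". That start is to be randomised only if feasible, and probably for the opportunistic offer alone.

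**The concern.** Three problems meet on one endpoint.

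- **Status.** A primary endpoint in one section is secondary in another. The promised multiplicity adjustment has no defined scope until this is settled.
- **Trend.** A test with only a before/after factor cannot tell an intervention effect from whatever coverage would have done anyway. Recruitment lasts 6 to 12 months per practice, so drift also accrues over windows of unequal length.
- **Standard error.** With a look-back of 3.5 or 5.5 years and readings a year or less apart, most women are counted in both readings, usually with the same status. Mantel-Haenszel treats the two readings as independent samples. Stratifying by practice removes differences in level between practices, but it assumes a common change.

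At stake is the coverage half of the primary objective, which is meant to inform policy on self-sampling.

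**Working it through.** **Plan's own figures.** The protocol gives no precision or power for coverage, so there is nothing to reproduce for that endpoint. The inputs borrowed below (106 practices, 9 months on average) do reproduce its mail-out number: 106 × 20 × 9 = 19,080, against about 19,000 in section 9.1.1.

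**Eligible women.** Section 5 gives coverage and practice counts for five CCGs. The practice-weighted mean is (33×54.6 + 33×62.8 + 57×63.0 + 36×60.9 + 53×62.9)/212 = 61.3%. Section 9.1 gives 190,579 overdue women. The denominator is therefore 190,579/(1 − 0.613) ≈ 492,000, or about 246,000 in 106 practices (about 2,320 each). Weighting by practice instead of list size is an assumption.

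**Scale of the effect.** Expected returns are 10,000 (summary) to 11,300 (2,800 + 8,500, sections 9.1.1 and 9.1.2). If every return were HPV negative and newly covered, coverage would rise by 10,000/246,000 = 4.1 to 11,300/246,000 = 4.6 points. That is a ceiling.

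**Naive standard error.** √[2p(1−p)/n] = √[2 × 0.613 × 0.387/246,000] = 0.139 points.

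**Drift with no intervention effect** (drift sizes are assumptions):

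| Drift (points) | z = drift/0.139 | Chance of rejection, independent samples |
|---|---|---|
| 0.25 | 1.80 | 44% |
| 0.5 | 3.60 | 95% |
| 1.0 | 7.20 | about 100% |

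Overlap between the readings does not remove this. With the SD of z cut to 0.45 (see the next table), a drift of 0.25 is still rejected with probability P(Z > (1.96 − 1.80)/0.45) = P(Z > 0.36) = 36%. At 0.5 points, simulated rejection ran from about 84% to 100% over all settings of overlap and between-practice variation tried.

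**Type I error with no drift and zero mean change** (2,000 simulations, 106 practices, practice-stratified test; correlation and SD are assumptions):

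| Within-woman correlation | SD of practice changes | SD of z | Rejection |
|---|---|---|---|
| 0 | 0 | 0.98 | 4% |
| 0.8 | 0 | 0.45 | 0% |
| 0.9 | 0 | 0.32 | 0% |
| 0 to 0.9 | 1 point | 1.23 to 0.78 | 10% to 1% |
| 0 to 0.9 | 2 points | 1.76 to 1.43 | 26% to 17% |

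Overlap alone makes the test conservative. Variation between practices makes it liberal. A t-test on practice-level differences holds about 5% in every row, but it does not remove drift.

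**Effect on the estimate.** Take a drift of 1 point a year and a mean exposure of 9 months. The bias is 1 × 9/12 = 0.75 points. A true gain of 4.0 points then reads as about 3.2 if coverage is falling and 4.8 if it is rising. In simulation with starts staggered over 6 months, a model with practice and calendar-month effects and exposure since start returned 4.0 in both cases, and 0.0 when there was no effect. That check assumes the exposure term has the right shape and that the whole intervention is staggered.

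**The case against.** **This is an estimation and feasibility study, and the test is exploratory.** Section 9.1 disclaims power calculations, and section 9.2 leaves detail to a statistical analysis plan that is not among the documents. That stands as far as model detail goes. It does not settle which endpoints are primary, which the protocol fixes two ways, nor the named test, which it also fixes. A trend biases the estimate as well as the p-value.

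**Time is not ignored altogether.** Monthly coverage, a second baseline, the four pre-trial months used for the third primary endpoint and a historical cohort (section 4.1.2) are all planned. That also stands. The gap is that none of them is tied to the coverage analysis. A baseline one year before the end deals with season but not with trend.

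**Clustering may mean a robust, cluster-adjusted version of the test.** If so, the standard-error point weakens considerably. The trend point does not.

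A reader might infer three stronger claims that the documents do not support:

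- **That randomised start dates are being thrown away.** Randomisation is conditional, likely confined to the opportunistic offer, and excludes early-adopter practices. Section 4.1.1 speaks of a possible temporal trend but does not cite falling coverage as its reason.
- **That the subgroup test ignores change.** The sentence beginning "We will also explore whether coverage varies as a function of age group, screening history, ethnic group and LSOA" goes on to name change in coverage as the quantity. Its wording is unclear, but it does not omit change.
- **That the inequalities objective is undermined.** Section 3.2 defines that objective on kit uptake, and section 9.2.2 analyses uptake with time-adjusted mixed models.

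**Conclusion.** The point holds in this form. The endpoint hierarchy contradicts itself. The one test named for coverage counts secular trend as effect, and unless the clustering phrase means more than stratification, its standard error is wrong in a direction that cannot be known in advance.

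The contradiction and the missing time term rest on the text alone. The sizes are illustrative. They depend on an assumed drift (0.25 to 1 point), within-woman correlation (0 to 0.9), between-practice SD (0 to 2 points) and practice-weighted coverage, and the protocol gives no rate of decline. Against a ceiling of 4.1 to 4.6 points, a bias of 0.75 points would matter.

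The finding should not be read as predicting a false success. If coverage keeps falling, as section 1 describes, before/after understates benefit, and with no effect the test would show a significant fall. Overstatement would need a rising trend.

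**What to change.** 1. Use one endpoint hierarchy. State in sections 3.2 and 9.2 whether change in coverage is primary, place all three listed endpoints accordingly, and say which of them the multiplicity adjustment covers.
2. Replace the Mantel-Haenszel test with a practice-month model of coverage. Include practice and calendar-month effects, exposure since each practice's start, and either practice-clustered standard errors or a random practice-by-exposure effect. Report the change with a 95% CI, and say what role each of the two baselines has.
3. State what the model identifies. Randomised starts, if used, identify only the opportunistic component. Mail-out may begin almost immediately (section 4.1), which would leave its effect nearly inseparable from calendar month. Without randomised starts the estimate is time-adjusted but not randomised. It should not be presented as a stepped-wedge estimate of the mail-out or total effect.
4. If change is to be compared between subgroups, use a period-by-group term.

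The cost is wording in the protocol and analysis plan. Practice-specific monthly coverage is already to be collected (sections 9.2.3 and 10.4.1). Only the subgroup comparison needs more: coverage counts by group. Because coverage is supplied as practice aggregates, a paired analysis by woman is not available from those data.

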| Trial Duration      | 
Set-up period: 3-6 months (staggered at each GP practice)
 
Active recruitment of participants: 6-12 months at each GP practice (average 9 months)
 
Clinical Follow up: 6 months after end of recruitment for follow up data on all women who are HPV positive on self-sample (clinical outcome assessment)
 
Analysis: 3 months
 
Total: 21 months
                                                                                                                                                                                                                                                                                                                                                                                              |                 |
| Objectives          | Objective                                                                                                                                                                                                                                                                                                                                                                                                                                                                                                                                                                                                                                                                                                                                                                                                       | Outcome measure |

|                                                          |                                                                                                                                                                                                   |                                                                                                                                                                                                                                                                                                                         |

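### The Mantel-Haenszel test planned for coverage before versus after does not say how it handles clustering; with practice as stratum, the likelier reading, its p-value is miscalibrated in an unknown direction

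*Protocol*

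**What the plan says.** Protocol Section 3.2 lists the change in coverage as the second primary endpoint and defines it within practice: "The endpoint is the change in coverage from the (practice-specific) beginning to the (practice-specific) end of the trial (all NHAIS data". A woman counts as covered if she was screened "in the past 3.5y if aged 25-49 or 5.5y if aged 50-64y as a % of all those eligible for cervical screening". The Trial Summary puts recruitment at 6 to 12 months per practice, 9 on average. Section 9.2.3 adds a second baseline, one year before the trial ends.

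The analysis stands in Section 9.2.3, under secondary outcomes: "We will run a Mantel-Haenszel test accounting for clustering at the GP practice level to explore the relationship between coverage and before/after". The next sentence plans to compare the change across age group, screening history, ethnic group and LSOA, "using the extended Mantel-Haenszel test for 2\*j tables so to account for the clusters". Neither sentence gives a variance formula, mentions pairing of women or periods, or plans a confidence interval for the change in coverage.

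Section 10.4.1 supplies coverage as anonymous aggregate data: "Practice-specific coverage at before study start, monthly and at the end of the trial". Line-level NHAIS data are planned only for women at least 6 months overdue.

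**The concern.** A Mantel-Haenszel test stratified by practice uses one two-by-two table per practice: before or after against covered or not covered. Stratifying removes differences between practices in baseline coverage. It leaves two problems.

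- **The rows are not independent.** With a look-back of 3.5 or 5.5 years and snapshots no more than about a year apart, most women, and most of the tests that make them covered, appear in both rows. The standard variance ignores this positive correlation and is too large.
- **Practices will not all change by the same amount.** Recruitment periods differ, starts are staggered (Section 4.1), and the opportunistic offer is left to the discretion of the health professional (Section 7.2.2). Section 9.2.3 itself plans funnel plots to look at variation across practices. The standard variance contains no term for this and is too small.

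At stake are the p-value of the only test named for a listed primary endpoint and any statement of precision drawn from it. Section 9.1 presents the trial as one that estimates the increase in coverage, so precision is a main product.

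**Working it through.** The protocol states no SE, interval, power or p-value for the coverage comparison, so there is no figure to reproduce.

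**Inputs from the protocol**
- 212 practices, 190,579 overdue women, 106 practices expected (Section 9.1).
- Coverage by CCG (Section 5): Camden 54.6% (33 practices), Islington 62.8% (33), Barnet 63.0% (57), Tower Hamlets 60.9% (36), Newham 62.9% (53).
- Expected returns: about 2,800 by mail-out (Section 9.1.1) and about 8,500 opportunistically (Section 9.1.2).

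**Assumptions, not in the protocol**
- Share f of women in both snapshots: 0.9 (range 0.6 to 1.0).
- Share d of these who change status: 0.15 (range 0.10 to 0.30).
- SD of the true change between practices: 0 to 3 points.

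**Step 1, denominator.** Practice-weighted coverage = (33×54.6 + 33×62.8 + 57×63.0 + 36×60.9 + 53×62.9)/212 = 61.3%. Women in 106 practices = 190,579/(1 − 0.613)/2 ≈ 246,000, or about 2,320 per practice.

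**Step 2, SE if the snapshots were independent.** √(2 × 0.613 × 0.387/246,000) = 0.139 points.

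**Step 3, overlap.** Within-woman correlation ρ = (p − d/2 − p²)/(p(1 − p)) = 1 − 0.075/0.237 = 0.68. True SE / independent SE = √(1 − fρ) = √(1 − 0.9×0.684) = 0.62, so the true SE is 0.086 points if all practices change equally. Over the full ranges of f and d the ratio runs from 0.46 to 0.88.

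**Step 4, spread between practices.** True SE = √(0.086² + SD²/106). Size of a nominal 5% test = 2 × [1 − Φ(1.96 / ratio)], where ratio = true SE / 0.139.

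| SD of practice change (points) | True SE (points) | Ratio | Size |
|---|---|---|---|
| 0 | 0.086 | 0.62 | 0.16% |
| 1 | 0.130 | 0.93 | 3.6% |
| 2 | 0.212 | 1.53 | 20% |
| 3 | 0.304 | 2.19 | 37% |

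The two errors cancel at SD = √(106 × (0.139² − 0.086²)) ≈ 1.1 points.

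**Step 5, simulation.** Trials of 106 practices with no mean change gave the same pattern. With the assumptions above, the stratified test rejected in about 0.1-0.2% at SD 0, about 3-5% at SD 1, about 20-24% at SD 2 and about 36-42% at SD 3. With overlap of 70-90% and status change of 15% or 25%, the ranges were 0.15-1.7%, about 3-8%, about 20-23% and about 37-39%. In those settings a paired t-test on practice changes, and a Mantel-Haenszel test with a practice-robust variance, both held 4.4-5.6%. A size-weighted practice-level analysis held about 4-6%, also with unequal practice sizes.

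**Step 6, scale.** (2,800 + 8,500)/246,000 = 4.6 points at most. That is 4.6/0.139 ≈ 33 independent-samples SEs, and 4.6/0.212 ≈ 22 of the true SEs at SD 2.

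**The case against.** The strongest reply is that the protocol does not say the test is only stratified. Its reference to clustering could mean a variance that keeps both periods of a practice together, and that version holds its level. The 2×j sentence, with its "so to account for the clusters", describes a different analysis, and Section 9.2 leaves detail to the statistical analysis plan. This stands in part. The wording makes stratification likelier, and Section 9.2.2 names a random effect for practice where one is meant, but the matter is not settled. The point is therefore conditional.

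Three further replies also carry weight:

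- **No interval is planned for the coverage change.** A reader might infer that a stated confidence interval is wrong. The protocol contains none, so only the p-value, and any interval later built on the same variance, is in question.
- **The overlap of women makes the test conservative.** A reader might infer that repeated women produce false positives. They do not; the inflated rates come from the spread between practices alone. Under a strict null of no change in any practice, the spread is zero. The inflated rates concern the average change over a wider set of practices. That is nevertheless the relevant question for a trial meant to inform wider roll-out (Section 2), and background trends can differ between practices without any intervention.
- **Practice-level description is already planned.** Section 9.2.3 lists the change at each practice, monthly coverage and funnel plots. What is missing is a summary change with a valid standard error.

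The reply that Section 9.2.3 only explores carries less weight, because Section 3.2 lists the change in coverage as a primary endpoint.

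**Conclusion.** The point holds conditionally. If practice enters only as stratum, the planned p-value is miscalibrated, and its direction depends on a spread that the protocol does not give. At 90% overlap and 15% status change the test is far too conservative with no spread, close to nominal at an SD of about 1 point, and rejects about four times too often at 2 points. These rates rest on assumed overlap, turnover and spread; only the denominator and the number of practices follow from the protocol.

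A reader might go further and conclude that the coverage result could not be trusted or would be reversed. The figures do not support that: a change near 4.6 points would be significant under either variance. The consequences are mainly for the precision reported, for small changes and possibly for the subgroup comparisons, which were not simulated.

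**What to change.** In Section 9.2.3, and correspondingly in the statistical analysis plan:

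1. Name the practice as the unit of analysis for the change in coverage.
2. Estimate the mean practice-level change, end minus start, weighted by the number of eligible women, with a 95% CI from the between-practice or practice-robust variance.
3. Either drop the Mantel-Haenszel test or state that its variance keeps both periods of a practice in one cluster. Apply the same rule to the extended test for the subgroups.

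The cost is a few sentences. The practice-specific coverage at start and end is already in the planned NHAIS extract (Section 10.4.1). Matching individual women over the whole denominator is not possible with the planned data, and this analysis does not need it.
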